## Abstract

**Background:**

Evidence from epidemiological and animal studies support the concept of programming fetal, neonatal, and adult health in response to in utero exposures such as maternal obesity and lifestyle variables. Excess gestational weight gain (GWG), maternal physical activity, and sub-optimal and excess nutrition during pregnancy may program the offspring’s risk of obesity. Maternal intake of dairy foods rich in high-quality proteins, calcium, and vitamin D may influence later bone health status. Current clinical practice guidelines for managing GWG are not founded on randomized trials and lack specific “active intervention ingredients.” The Be Healthy in Pregnancy (BHIP) study is a randomized controlled trial (RCT) designed to test the effectiveness of a novel structured and monitored Nutrition + Exercise intervention in pregnant women of all pre-pregnancy weight categories (except extreme obesity), delivered through prenatal care in community settings (rather than in hospital settings), on the likelihood of women achieving recommended GWG and a benefit to bone status of offspring and mother at birth and six months postpartum.

**Methods:**

The BHIP study is a two-site RCT that will recruit up to 242 participants aged > 18 years at 12–17 weeks of gestation. After baseline measures, participants are randomized to either a structured and monitored Nutrition + Exercise (intervention) or usual care (control) program for the duration of their pregnancy. The primary outcome of the study is the percent of women who achieve GWG within the Institute of Medicine (IOM) guidelines. The secondary outcomes include: (1) maternal bone status via blood bone biomarkers during pregnancy; (2) infant bone status in cord blood; (3) mother and infant bone status measured by dual-energy absorptiometry scanning (DXA scan) at six months postpartum; (4) other measures including maternal blood pressure, blood glucose and lipid profiles, % body fat, and postpartum weight retention; and (5) infant weight z-scores and fat mass at six months of age.

**Discussion:**

If effective, this RCT will generate high-quality evidence to refine the nutrition guidelines during pregnancy to improve the likelihood of women achieving recommended GWG. It will also demonstrate the importance of early nutrition on bone health in the offspring.

**Trial registration:**

ClinicalTrials.gov, NCT01689961 Registered on 21 September 2012.

**Electronic supplementary material:**

The online version of this article (10.1186/s13063-018-3065-x) contains supplementary material, which is available to authorized users.

## Background

### Consequences of excess gestational weight gain (GWG)

The documented adverse sequelae of excess GWG for both mother and child include undesirable pregnancy/birth outcomes and/or later health outcomes that are likely to impose a substantive downstream burden on healthcare costs [1]. The most common adverse effect of excessive GWG on maternal health is weight retention (five months and even up to three years postpartum) [2–4]. Mothers entering subsequent pregnancies at a higher weight are at greater risk for long-term obesity and future co-morbidities such as diabetes and cardiovascular disease [5, 6]. The emerging evidence of developmental origins of health and disease implicates the impact of mothers’ health during pregnancy on “programming” of the growing fetus in utero to develop adverse health outcomes [7, 8]. Maternal excess GWG has been reported as the strongest predictor of obesity in the offspring [9–11].

The use of low-fat dairy foods as the source of protein in pregnancy is proposed based on studies in animals [12] and humans [13–15] that provide support for the putative effects of components of dairy foods such as calcium and leucine as anti-adipogenic and pro-lipolytic agents. Consumption of high dairy protein may not only benefit GWG but also improve other maternal pregnancy outcomes such as dysglycemia, elevated blood pressure, blood lipid profiles, and risk of pre-eclampsia, the latter due to higher intake of calcium and vitamin D [16].

Guidelines for GWG exist and have been interpreted for practice in Canada [17, 18]. Until there is evidence of effective population level interventions to assist women in achieving healthy weights, programs aimed at interventions during pregnancy to improve weight management and pregnancy outcomes are a starting point. Pregnancy has been described as a “teachable moment” for weight control and obesity prevention in women [19]. The most convincing approach to achieve reduction in GWG is the combination of physical activity and diet counseling, preferably in combination with weight monitoring [1, 20, 21]. Yet current clinical practice guidelines for managing GWG are not founded on randomized trials and lack specific “active intervention ingredients” [21] that are proven effective in achieving target GWG.

### Maternal programming of bone health

Findings from epidemiological and animal studies support a role for the programming of fetal, neonatal, and adult bone outcomes in response to exposures during pregnancy such as maternal nutrition and other lifestyle variables [22–25]. In three longitudinal observational studies, maternal intake of dairy foods during pregnancy was associated with higher bone mass in offspring aged 6–16 years [26–28]. In prospective cohort studies, maternal physical activity level has also been positively associated with infant bone mass and geometry at birth [29, 30]. Being born with optimal bone mass may have long-term benefits since childhood bone mass tracks until skeletal maturity, when peak bone mass is achieved [31]. Collectively, these findings suggest that bone mass during childhood and adolescence may be predictive of an individual’s risk for osteoporosis, as peak bone mass is a strong predictor of osteoporotic fracture later in life [32].

To date, only one randomized controlled trial (RCT) in a small sample (*N* = 36) investigated the effect of dairy product supplementation on bone mineral density (BMD) and bone turn-over in pregnant women and these women entered pregnancy with a habitually low calcium intake [33]. The study showed a beneficial effect of increased milk consumption on maternal bone mass density at the spine and on suppression of bone resorption when measured at 6 ± 1 weeks postpartum. While promising, further studies are needed with larger sample sizes and evaluation of bone health outcomes in the offspring. In addition, no study to date has investigated the impact of dairy product supplementation during pregnancy on bone health outcomes of women after delivery.

Informed by our recent clinical and qualitative research, as well as existing systematic reviews, we have designed a RCT comprising several unique features with the objective of controlling GWG and optimizing bone health of mother and infant. We will test the effectiveness of a novel structured and monitored nutrition (high-protein dairy-based diet) along with an exercise (walking) intervention that is science-based, vetted for feasibility in pregnant women and care providers through focus groups, in pregnant women of most pre-pregnancy weight categories (except extreme obesity) in a community setting (as opposed to hospital-based).

### Specific objectives and hypothesis

The primary research objective of the Be Healthy in Pregnancy (BHIP) study is to determine whether introducing a structured and monitored nutrition (high-dairy protein diet) and exercise (walking) program (intervention) in early pregnancy, compared to standard prenatal care (control), will increase the number of women attaining GWG (outcome) within the Institute of Medicine (IOM) recommendations for their pre-pregnancy body mass index (BMI) sub-category [17].

Secondary objectives include determination of the impact of a maternal high-dairy diet with exercise compared to standard care diet during pregnancy on: (1) bone status (e.g. blood biomarkers procollagen type I that contains N-terminal extensions (PINP), C-terminal telopeptide of type I collagen (CTX-I), insulin-like growth factor-1 (IGF-1), 25-hydroxyvitamin D (25(OH)D), and 1,25-dihydroxyvitamin D) in mothers during pregnancy; (2) infant bone status at birth via cord blood; and (3) mother and infant bone status at six months postpartum by dual energy x-ray absorptiometry (DXA) scan.

The over-arching hypothesis is that maternal consumption of a high-dairy diet during pregnancy will have a positive impact on: (1) GWG; (2) bone health status of the mother during and after pregnancy; and (3) bone mass and bone size of the offspring, after adjustment for factors known to influence skeletal status.

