## Methods/design

### Trial design

The BHIP study is a two-arm, two-site prospective RCT. This study is designed as a prospective superiority trial, with 1:1 allocation ratio to either the Intervention group (i.e. Nutrition + Exercise intervention: high-dairy nutrition intervention combined with structured exercise) or the Control group (i.e. usual care as per National Health Canada recommendations) during pregnancy. The study is open-label with blinded endpoints. The study protocol is described following the standard protocol items: recommendations for interventional trials (SPIRIT) guidelines [34]. See Additional file 1 for the SPIRIT checklist and Additional file 2 for the WHO trial registration data set.

The core BHIP trial follows women up to delivery as the primary outcome relates to GWG. The Bone-BHIP study is an extension of the core BHIP trial that continues a follow-up of the women and their offspring until six months after delivery, with the objective to assess maternal and infant bone status. This trial is registered at ClinicalTrial.gov (NCT01689961). The BHIP trial is conducted by collaborative research teams at McMaster University (Hamilton, ON) and Western University (London, ON) in Canada. The study takes place in academic hospitals and community healthcare clinics in London, Burlington, and Hamilton, Ontario, Canada. Recruitment is facilitated by healthcare professionals (e.g. family doctors and midwives) who ask their patients for consent to be contacted by the BHIP study team, as well as poster advertisements in midwifery, family practice, and ultrasound clinics, at community sites such as the YMCA, libraries, and coffee shops, and on Facebook or Kijiji.

Study recruitment began in January 2013 and is expected to be completed by April 2018, reaching the a priori calculated sample size of 242 participants for our primary outcome. All participants who sign consent to contact forms receive a phone call by study personnel and are provided a general overview of the study and expectations using a scripted text. Figure 1 outlines the participant’s timeline in the BHIP study. Participants are screened for eligibility during the telephone interview according to the criteria list below. Eligible women are enrolled in the study and sign informed consent by the end of the first trimester of pregnancy (i.e. 12–17 weeks of gestation).

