## Outcome measurements

Primary and secondary outcomes are summarized in Table 2 and described below.Primary outcome○ GWGSecondary outcomes○ Maternal and cord blood circulating bone markers: PINP, CTX-I, IGF-1, 25(OH)D, 1,25dihydroxyvitamin D○ Maternal bone status at six months postpartum: whole-body bone mineral content (BMC), whole body BMD, lumbar spine BMD○ Infant bone status at six months of age: whole body minus the head BMCOther outcomes○ Maternal body weight and fat mass○ Maternal metabolic status (including fasting glucose and lipid profiles, leptin and adiponectin)○ Maternal blood pressure○ Maternal pregnancy outcomes such as gestational diabetes and pre-eclampsia○ Infant birth outcomes such as birth weight and body fat mass at six months○ Safety outcomes○ Quality of life using the EQ-5D questionnaire○ Healthcare costs○ Maternal and cord blood gene variant profiles

**Table 2 Tab2:** Analysis plan: objectives, outcomes, hypotheses, and methods of analysis

Objective	Hypothesis	Outcome measure (type of outcome: B = binary or C = continuous)	Methods of analysis
1. Primary	An experimental combined Nutrition + Exercise intervention will increase the percentage of pregnant women who achieve GWG within current recommendations when compared with standard care provided in the primary care community setting	Proportion of women who are within the BMI appropriate GWG according to the IOM guideline for GWGs (B)	Logistic regression
2. Secondary	An experimental combined Nutrition + Exercise intervention will lead to better maternal and child bone health outcomes when compared to standard care	*• Maternal and cord blood circulating bone markers (C)* ○ Bone biomarkers: PINP, CTX-I, IGF-1, 25(OH)D, 1,25(OH)_2_D *• Maternal bone status at 6 months postpartum (C)* ○ Whole body bone mineral content, whole body BMD, lumbar spine bone mineral density by DXA scan *• Maternal fat mass (C)* *• Maternal blood glucose, lipid profile, leptin, and adiponectin* *• Maternal blood pressure (C)* ○ Diastolic BP ○ Systolic BP *• Maternal pregnancy outcomes (B)* ○ Gestational diabetes ○ Pre-eclampsia *• Infant bone status at 6 months of age (C)* ○ Whole body minus the head bone mineral content by DXA scan *• Infant outcomes* ○ Birth weight z-score(C) ○ Body fat mass (B)	Regression analysis *We will use logistic regression for binary outcomes and linear regression for continuous outcomes

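### The over-arching hypothesis and the planned conclusions credit nutrition, but the two-arm design identifies only the joint effect of diet, walking and extra contact

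*Protocol article*

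**What the plan says.** Under Specific objectives and hypothesis, the protocol article states as its over-arching hypothesis that "maternal consumption of a high-dairy diet during pregnancy will have a positive impact on" three things, namely GWG, the mother's bone health, and the bone mass and size of the offspring. Walking does not appear in that sentence.

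The expected conclusions lean the same way. The Discussion part of the Abstract says the trial will help refine nutrition guidelines so that more women reach recommended GWG, and adds: "It will also demonstrate the importance of early nutrition on bone health in the offspring". The last paragraph of the main Discussion again names nutrition guidelines, this time with skeletal benefit included. Neither place mentions exercise.

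The design is stated under Trial design: "The BHIP study is a two-arm, two-site prospective RCT". The experimental arm is described as "Nutrition + Exercise intervention: high-dairy nutrition intervention combined with structured exercise".

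Table 2 words its hypotheses for the package. For the bone outcomes it reads: "An experimental combined Nutrition + Exercise intervention will lead to better maternal and child bone health outcomes". The primary and secondary objectives, in the same section as the over-arching hypothesis, also name diet and exercise together.

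**The concern.** A claim about diet needs a contrast in which diet differs and other plausible causes do not. Here the arms also differ in walking and in the amount of contact with study staff. The article itself supplies walking as a rival explanation for the infant outcome. Under Maternal programming of bone health it notes that "maternal physical activity level has also been positively associated with infant bone mass and geometry at birth". For GWG, the Background calls the combination of activity and diet counselling, preferably with weight monitoring, the most convincing approach.

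What is at stake is the claim made from a positive result. If the over-arching hypothesis and the conclusions stay as worded, a difference between arms could enter nutrition guidance as evidence for dairy or early nutrition, although walking, contact or the combination could have produced it. A null result would not refute the dairy hypothesis either, since it too speaks only to the package.

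**Working it through.** The article gives no figure for this point, so the check is one of identifiability.

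**Inputs, all from the protocol article**
- Two arms, allocated 1:1 (Trial design). The target of 242 (Power calculation) gives 242 / 2 = 121 per arm.
- Intervention arm: high-protein dairy plan, controlled walking and 10,000 steps per day (Table 1); weekly or biweekly counselling; nutrition plan modified according to monitored weight gain (Interventions).
- Control arm: usual prenatal care and Health Canada materials. All participants in both arms receive study-nutritionist counselling on Health Canada advice (Interventions).
- No arm receives the diet without the walking, or the walking without the diet.

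**Step 1: what the contrast estimates.** Let D = 1 for the dairy plan, W = 1 for the walking programme and C = 1 for the extra contact and weight monitoring. Without interactions, the mean outcome (on the log-odds scale for GWG within guidelines) is

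b0 + bD·D + bW·W + bC·C.

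Control has D = W = C = 0 and intervention has D = W = C = 1. The difference between arms is bD + bW + bC, plus any interaction terms. It is one number and cannot be split.

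**Step 2: rank.** Take only intercept, D and W. The rows are (1, 0, 0) for 121 women and (1, 1, 1) for 121 women. The D and W columns are identical, so the matrix has 3 columns and rank 2. More women only repeat the same two rows, so the rank stays at 2. For reference, a 2×2 layout has rows (1, 0, 0), (1, 1, 0), (1, 0, 1) and (1, 1, 1), with rank 3, and would identify separate additive effects.

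**Step 3: illustration.** Take the 30-point difference mentioned under Power calculation, purely as an example and ignoring contact. Diet 30 + walking 0, 15 + 15, 0 + 30, and 40 + (−10) all sum to 30 and predict the same data in the two arms.

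**Step 4: does the planned analysis help?** Statistical methods specifies logistic or linear regression that accounts for site and BMI category. These covariates do not separate D from W, because D = W within every stratum. The over-arching hypothesis also refers to adjustment for factors that influence skeletal status. Step counts during the intervention are recorded in all participants, but they are measured after randomisation and are themselves targeted by the intervention. Conditioning on them gives a non-randomised comparison that rests on further assumptions.

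**The case against.** The strongest reply is that every operative statement already concerns the package. The primary objective, the secondary objectives and the Table 2 hypotheses all name diet with exercise. No analysis, alpha or sample size is tied to a dairy-only hypothesis. Comparing a multicomponent programme with usual care is a legitimate choice, which the Background motivates. On this view the over-arching hypothesis is shorthand for the rationale, and refining nutrition guidelines is an intended use, conditional on the programme working.

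Most of this stands, and it limits the point to attribution. It does not remove it: the sentence is presented as the hypothesis, covers all three outcome groups, and is echoed by conclusions that leave out exercise.

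Several stronger readings are not supported:
- A reader might infer that the trial tests the wrong hypothesis or that its primary analysis is invalid. The objectives and Table 2 show otherwise.
- A reader might infer that the conclusions name dairy, or that the whole Discussion credits diet. The conclusions say nutrition, and the opening of the Discussion names the combined intervention and describes both components.
- A reader might infer that controls receive no counselling. They receive study-nutritionist counselling on Health Canada advice and are invited to a focus group and a midwife-led session. The difference is in continuing contact and the structured programme.
- A reader might bound the diet share between 0% and 100%. That assumes neither component does harm and that they do not interact, and the documents establish neither.

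**Conclusion.** The point holds as a fault of attribution. The over-arching hypothesis, and the conclusions in the Abstract and the last paragraph of the Discussion, claim something about nutrition that randomisation in this trial cannot show. The separate effect of diet is unidentified at any sample size, so no percentage can be put on its share. This rests only on the arms differing in diet, walking and contact together, as Table 1 and Interventions describe. Analyses of food records or armband data could address the components under extra assumptions, but not as randomised evidence. The comparison of the combined programme with usual care is valid and unaffected, and so is its power. The correction is worth making because it changes what the trial may claim to those who write guidelines.

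**What to change.** - Specific objectives and hypothesis: replace the over-arching hypothesis with the Table 2 wording, that is, the combined Nutrition + Exercise programme compared with usual care, for GWG and for maternal and offspring bone.
- Discussion part of the Abstract, and last paragraph of the main Discussion: limit the conclusions on GWG and bone to the combined programme.
- Label any diet-specific or step-specific association, from food records or armband data, as exploratory and non-randomised.

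The opening of the main Discussion, the design and the sample size need no change. The cost is an edit to the text and a less specific headline claim.

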## Methods/design

### Trial design

The BHIP study is a two-arm, two-site prospective RCT. This study is designed as a prospective superiority trial, with 1:1 allocation ratio to either the Intervention group (i.e. Nutrition + Exercise intervention: high-dairy nutrition intervention combined with structured exercise) or the Control group (i.e. usual care as per National Health Canada recommendations) during pregnancy. The study is open-label with blinded endpoints. The study protocol is described following the standard protocol items: recommendations for interventional trials (SPIRIT) guidelines [34]. See Additional file 1 for the SPIRIT checklist and Additional file 2 for the WHO trial registration data set.

The core BHIP trial follows women up to delivery as the primary outcome relates to GWG. The Bone-BHIP study is an extension of the core BHIP trial that continues a follow-up of the women and their offspring until six months after delivery, with the objective to assess maternal and infant bone status. This trial is registered at ClinicalTrial.gov (NCT01689961). The BHIP trial is conducted by collaborative research teams at McMaster University (Hamilton, ON) and Western University (London, ON) in Canada. The study takes place in academic hospitals and community healthcare clinics in London, Burlington, and Hamilton, Ontario, Canada. Recruitment is facilitated by healthcare professionals (e.g. family doctors and midwives) who ask their patients for consent to be contacted by the BHIP study team, as well as poster advertisements in midwifery, family practice, and ultrasound clinics, at community sites such as the YMCA, libraries, and coffee shops, and on Facebook or Kijiji.

Study recruitment began in January 2013 and is expected to be completed by April 2018, reaching the a priori calculated sample size of 242 participants for our primary outcome. All participants who sign consent to contact forms receive a phone call by study personnel and are provided a general overview of the study and expectations using a scripted text. Figure 1 outlines the participant’s timeline in the BHIP study. Participants are screened for eligibility during the telephone interview according to the criteria list below. Eligible women are enrolled in the study and sign informed consent by the end of the first trimester of pregnancy (i.e. 12–17 weeks of gestation).

